### Data monitoring

Data will be monitored by the trial management committee at monthly intervals. Prior to analysis data entry checking will be conducted for accuracy on 10% of all participants, and queries resolved through discussion with the trial management committee and access to the source documents. Data management will adhere to the Physical Activity and Nutritional INfluences In ageing (PANINI) project data management plan, which was developed in accordance with national and European principles as part of the university research governance and European Commission research governance guidelines. Thus, data management for this project adheres to the Findable, Accessible, Interoperable, and Reusable (FAIR) principles.^49^

### Sample size

This study aims to recruit a convenience sample of n =~30 participants: 15 in each intervention. No formal power calculations were conducted due to the feasibility nature of this study. This sample size was based on initial expectations related to the obtainment of data saturation in the qualitative component of the study given its phenomenological approach.^50 51^

### Identification, consent and recruitment

#### Identification

Patients on the ward at the commencement of the study will initially be screened by their care team for the known presence of any severe sensory impairments which would exclude them from participation. Due to the study’s rolling recruitment, this initial screening will continue throughout the study as additional patients are admitted to the ward. Participant information sheets will not be distributed to patients who are deemed to be medically unfit or due for imminent discharge as identified by their care team. All other aspects of the screening process will occur after consent has been obtained. After identification, potential participants will be approached by the researcher with an information sheet related to the study and asked if they would be interested in participating, or if they would like to receive more information about the study (online supplementary file 2). The information sheet will contain all the most pertinent information relating to the study and specifically what it would require from potential participants. Potential participants will be given ≥24 hours to consider whether or not they would like to participate.

10.1136/bmjopen-2019-031159.supp2Supplementary data

#### Consent

At this stage, potential participants will also be provided with an informed consent form and asked if they would be interested in participating (online supplementary file 3). If it is deemed that a potential participant lacks the capacity to consent, a personal consultee will be sought. A personal consultee will be someone who cares for the patient, or is interested in their welfare (but not a paid professional), and who is prepared to be consulted and give advice on what they believe the patient’s wishes would be, were they to have the capacity to consent for themselves. If a personal consultee cannot be found, a nominated consultee will be sought. A nominated consultee will be someone who is familiar with the patient in a professional context and can adequately advise on whether they believe participation would be in the patients’ best interest. These processes will be informed by the UK Department of Health’s guidance on nominating a consultee for research involving adults who lack the capacity to consent^52^; in accordance with section 32^3^ of the Mental Capacity Act 2005.^53^ All efforts possible will be made in this regard to include participants whom lack the capacity to consent, as intrinsically within the research team from a personal and professional perspective we would consider it unethical to exclude potential participants from participating in a study, which can potentially benefit them and their overall health status, due to the fact that they lack the capacity to consent.

10.1136/bmjopen-2019-031159.supp3Supplementary data

#### Recruitment

Following consent being obtained from the participant themselves, or the obtainment of a declaration from a consultee, all consented participants will be screened for the remaining eligibility criteria.

### Statistical methods

#### Primary dependent variables

Analysis of the primary dependent variables will be based on an inductive process utilising Interpretative Phenomenological Analysis (thematic analysis). Two researchers will be employed to analyse the data to increase triangulation from the analysis perspective, having already triangulated data acquisition through obtainment from multiple sources (study participants and ward staff). All semi-structured interviews and focus groups will be audio recorded. Data synthesis will be performed through verbatim transcription. The three main steps of Interpretative Phenomenological Analysis will be followed^33^: (1) The generation of themes from transcripts within the areas of feasibility inquiry. As an iterative process, these themes will be continuously reviewed and adapted based on the emergence of information in subsequent transcripts. (2) The collation and separation of these themes within each of the areas of feasibility inquiry. (3) Written interpretation of the resultant themes within each of the areas of feasibility and their relationship to one another. At all stages within this process, reflective journal entries and field notes will be utilised to provide a more comprehensive understanding of the findings, in addition to incorporating additional feasibility information related to uptake and retention rates, and limited efficacy testing of the secondary dependent variables in the final analysis to provide a comprehensive assessment of the feasibility of the study.

#### Secondary dependent variables

Statistical analysis of the secondary dependent variables will be performed using IBM Statistical Package for Social Sciences (SPSS) software. These analyses will be performed as part of the limited efficacy testing regarding the potential impact of the interventions on the secondary dependent variables (proposed primary dependent variables of the future clinical trial). These analyse will provide an estimation of efficacy and provide valuable insight regarding feasibility; useful to informing the design of the future powered clinical trial. Specifically, the following statistical analysis will be utilised: 2×2 way independent measures analysis’ of variance consisting of two independent variables; the specially adapted resistance training intervention, and the MIOLI intervention, each with two levels: baseline and post-intervention. A subsequent post hoc test will be utilised if a significant main effect or interactions are found. Pearson product correlations will also be utilised between various sociodemographic variables (such as age and sex) and the dependent variables of this study, to assess possible relationships between differences in sociodemographic factors and changes in the dependent variables.

Central tendency and variability measurements consisting of parameters such as the mean, median and mode, and SD and range of scores, respectively, will also be utilised during the analysis of data for illustrative purpose. Significance levels will be set at 0.05 (p≤0.05), and effect sizes will be reported for all analyses. In order to establish if the assumptions of parametric statistics have been met regarding the assumption that there is a normal distribution of data, the data will be analysed for skewness and kurtosis. In the event, data do not fulfil the assumptions of parametric statistics, the non-parametric equivalent of the aforementioned statistical analysis will be employed, namely the Scheirer-Ray-Hare test, and Spearman’s rank-order correlations. As the quantitative component of this study has not been powered given the feasibility nature of the study, the examination of the efficacy of the intervention to impact these secondary dependent variables is limited; and interpretation of these results should be treated with caution pending the future powered clinical trial. All results will be reported with effect size and 95% CIs.

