### Design overview

This feasibility study will use a 2-week, interventional, independent measures research design (figure 1).

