**Figure 2 F2:**
[figure not shown]
The independent variables of the proposed future clinical trial.

In order to ensure this present study is as scientifically valid as possible a number of precautions have been taken to protect the internal and external validity of the study within its methodological design: first, for each participant, all testing procedures (baseline and post-intervention (2 weeks)) will be conducted at approximately the same time of day (±2 hours). This will be controlled in order to protect the findings of the study from changes in the dependent variables which may be attributable to circadian variation rather than manipulation of the independent variables.^29^ The hypothesis of the study will not be divulged to participants prior to or during the conduction of the study in order to control for any potential degree of demand characteristics; a scenario where participants alter their behaviour and/or answers, in order to align with what they believe is potentially the ‘desired’ outcome of the study. All dependent variable testing sessions will take place at least 24 hours after the cessation of the previous training session for each participant. This will be implemented to ensure acute fatigue does not become a contributing factor to the results of the study, specifically relating to the secondary dependent variables, but also the feasibility of such practice during a proposed future clinical trial. The order in which dependent variables are tested will be counter-balanced throughout the study at each assessment timepoint in order to attempt to protect the study from practice effects, especially order effects, where a participant has been exposed to a specific order of testing before and as such performs better on subsequent testing procedures of the same material. Additionally, only one intervention will be run at a given time, protecting against potential subconscious selection bias among the research team relating to group allocation of participants. Finally, in order to increase the external validity of the study, eligibility criteria will be kept as minimalistic as possible (within the limits of safety and reason), in order to allow as inclusive a proportion of this population as possible, and in such producing findings which are applicable to not only those within the study, but to the greater population of frail geriatric hospital inpatients and particularly those within delayed transfer of care settings.

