### Interventions

All participants will undergo 10 sessions in total throughout the 2-week intervention in either one of the two interventions. All session will be conducted individually under the guidance of a qualified trainer. A maximum of one session will be performed each day, and sessions will not be performed on any more than a maximum of three consecutive days throughout the duration of the study (table 2).

**Table 2 T2:** Study timeline of all major events during each round of recruitment (SPIRIT schedule)

Week	Seated physical activity in ageing (SPAA) study timeline						
	Monday	Tuesday	Wednesday	Thursday	Friday	Saturday	Sunday
0	Identification + participant information sheet distribution	24 hours consideration period	Recruitment, eligibility screening and baseline assessments	Recruitment, eligibility screening and baseline assessments	Recruitment, eligibility screening and baseline assessments	Recruitment, eligibility screening and baseline assessments	–
1	Training	Rest	Training	Training	Rest	Training	Training
2	Training	Rest	Training	Training	Training	Rest	Training
3	Post-intervention assessment	Post-intervention assessment	Post-intervention assessment	Post-intervention assessment	Post-intervention assessment	Post-intervention assessment	–

SPIRIT, Standard Protocol Items: Recommendations for Interventional Trials.

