### Data collection

Data will predominantly be collected at two main time points: baseline and post-intervention (table 2).

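### The pre-post efficacy outcomes are assigned to an independent-measures ANOVA with wrongly defined factors, so its tests and intervals for change use the wrong error term

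*Protocol article*

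**What the plan says.** The protocol article, under Statistical methods (Secondary dependent variables), names a "2×2 way independent measures analysis’ of variance consisting of two independent variables". It then defines these as "two independent variables; the specially adapted resistance training intervention, and the MIOLI intervention, each with two levels: baseline and post-intervention". If the normality checks fail, "the non-parametric equivalent of the aforementioned statistical analysis will be employed, namely the Scheirer-Ray-Hare test". A post hoc test follows a significant main effect or interaction. The significance level is 0.05, and effect sizes with 95% confidence intervals are promised for all results.

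Other sections describe the data structure:

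- Interventions: "All participants will undergo 10 sessions in total throughout the 2-week intervention in either one of the two interventions".
- Design overview: "for each participant, all testing procedures (baseline and post-intervention (2 weeks)) will be conducted at approximately the same time of day".
- Data collection: "Data will predominantly be collected at two main time points: baseline and post-intervention".
- Sample size: about 30 participants, 15 per intervention, with no power calculation.

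The analysis section states the purpose of these analyses: to estimate efficacy and help design the later powered trial.

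**The concern.** There are two separate faults in the one specification.

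First, the factors are mis-stated. The two interventions are two levels of a single factor. Baseline and post-intervention are the levels of a second factor, time. Crossing the factors as written would need a cell such as resistance training at baseline with MIOLI post-intervention, and nobody belongs in it. The model cannot be fitted literally.

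Second, an analyst who sensibly reads the sentence as arm by time is still told to use a between-participants ANOVA. About 60 values from about 30 people would be treated as 60 independent observations. The fallback does not help, because Scheirer-Ray-Hare is the rank version of the same between-participants layout. It is also only a test, so it supplies no interval for a change.

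At stake are the inferential results on the outcomes proposed as primary for the future trial. Intervals and variance-based effect sizes carried forward from this analysis would misstate how precisely change was estimated.

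**Working it through.** The article gives no power or sample-size figure to reproduce, so the check is whether the nominal 5% level and the interval widths hold.

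**Inputs from the article.** n = 15 per arm, 30 in total; two time points; alpha 0.05.

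**Assumptions.** Normal data with SD 1 at both times. Within-person correlation ρ is not stated and is taken as 0.3, 0.5, 0.7 and 0.8. The power illustration uses a true change of 0.4 SD in both arms. All figures adopt the charitable arm-by-time reading, since the literal one cannot be fitted.

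**Degrees of freedom.** Independent ANOVA: 4 × 15 − 4 = 56 for error, t = 2.003. Mixed ANOVA: 2 × 15 − 2 = 28, t = 2.048.

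**Mean change over time**
- As written: SE = √(2/30) = 0.258, so the half-width is 2.003 × 0.258 = 0.517 SD at every ρ.
- With pairing: SE = √(2(1 − ρ)/30). At ρ = 0.5 this is 0.183, so the half-width is 2.048 × 0.183 = 0.374 SD.
- Ratio at ρ = 0.5: 0.517 / 0.374 = 1.38.

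**Between-arm difference in change**
- As written: SE = √(4/15), half-width 1.034 SD.
- With pairing: SE = √(4(1 − ρ)/15), half-width 0.748 SD at ρ = 0.5. The ratio is again 1.38.

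The standard errors alone differ by 1/√(1 − ρ), which is 1.41 at ρ = 0.5. The interval ratio is slightly smaller because the two analyses use different t quantiles.

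**Arm main effect** (average of the two time points)
- As written: SE = √(2/30) = 0.258.
- Correct: SE = √((1 + ρ)/15), which is 0.316 at ρ = 0.5. The SE used is 0.816 of the correct one.

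**Results** (rejection rates and as-written power from simulation; interval widths from the formulas above)

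| ρ (assumed) | 0.3 | 0.5 | 0.7 | 0.8 |
|---|---|---|---|---|
| Half-width for change, as written (SD) | 0.517 | 0.517 | 0.517 | 0.517 |
| Half-width for change, paired (SD) | 0.443 | 0.374 | 0.290 | 0.237 |
| Width ratio | 1.17 | 1.38 | 1.79 | 2.19 |
| Time or interaction test, null rejection | 2% | 0.7% | 0.1% | 0.01% |
| Arm main effect, null rejection | 8% | 11% | 13% | 14% |
| Power for 0.4 SD change, as written | 30% | 27% | 23% | 19–20% |
| Power for 0.4 SD change, paired | 43% | 56% | 78% | 92% |

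At ρ = 0 the as-written tests reject 4.9%, so the method itself is sound for independent data. The mixed ANOVA stays between 4.6% and 5.2% for all three tests at every ρ from 0 to 0.9. Scheirer-Ray-Hare fails in the same way: at ρ = 0.7 it rejects 0.1% for time, 0.1% for interaction and 13.2% for arm.

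**The case against.** The strongest reply is about consequence. The primary analysis is qualitative, the sample size rests on data saturation, and the article calls the efficacy testing limited, unpowered and to be read with caution. No progression rule hangs on these p-values. That limits the harm, and it stands. It does not cure the fault: the caution concerns lack of power, and the wrong error term lowers power further.

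The label "2-week, interventional, independent measures research design" in Design overview is also defensible. Each person receives one intervention, so the comparison of interventions is between independent groups. The error lies in the analysis paragraph, not in that label.

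Three stronger readings are tempting, and the document does not support them:

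- A reader might infer that everything in the quantitative analysis is wrong. Point estimates of mean change, the descriptive statistics and the sociodemographic correlations do not use this error term and are unaffected.
- A reader might infer that the plan will produce false claims of benefit. With positive correlation the tests that bear on efficacy (time, and arm by time) become too conservative. Only the arm main effect is anti-conservative. It averages baseline and post-intervention values, so it is not the test of a treatment effect.
- A reader might infer that post hoc testing is pointless with two-level factors. That is so after a main effect. The article also allows it after an interaction, where looking at change within each arm is legitimate.

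Finally, no correlation is given. It may well be lower for some hormones, cytokines or questionnaires than for strength or function, so the low end of the range belongs in the picture. At 0.3 the loss is modest.

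**Conclusion.** The specification is wrong as written, and nothing elsewhere in the article repairs it. The factors cannot be crossed as stated, and both the ANOVA and its rank fallback ignore that each person is measured twice.

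On the arm-by-time reading, the ANOVA tests, their confidence intervals and variance-based effect sizes for change are incorrect at any non-zero within-person correlation. Over assumed correlations of 0.3 to 0.8, intervals for change are 1.17 to 2.19 times too wide, and power for an assumed 0.4 SD change falls from 43–92% to 30–19%. Zero correlation, the only case in which the method is valid, is implausible for the same person about two weeks apart.

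The exact sizes depend on the assumed correlation, normality, equal SDs and full data on 15 per arm. The direction needs only a positive correlation. The consequence is limited to the secondary limited-efficacy results and to what the future trial's design takes from them.

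**What to change.** Replace the ANOVA sentence with one along these lines: a mixed (split-plot) 2×2 ANOVA with time (baseline, post-intervention) as the within-participant factor and intervention as the between-participant factor, reporting the mean paired change in each arm and the between-arm difference in change, each with a 95% CI.

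Restrict post hoc testing to simple effects after a significant interaction.

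In place of "namely the Scheirer-Ray-Hare test", name the Wilcoxon signed-rank test for change within each arm and the Mann-Whitney test on change scores between arms. Give the intervals that correspond to these tests, so that the promised 95% CIs can be reported on this route too.

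The cost is the rewording of one paragraph. SPSS, the software already named, fits the mixed ANOVA as a standard procedure. No assessment, participant or data item changes.

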Limited-efficacy testing	Is 2 weeks a sufficient duration to potentially provide significant benefit to patients? Can intensive (5–6 days/week), short duration (2 weeks) physical activity interventions improve markers of multidimensional health, in very frail individuals?	Analysis of the secondary dependent variables within the study (primary dependant variables of the future clinical trial). Analysis of uptake and adherence rates. Analysis of the level of satisfaction with the interventions through questionnaires with participants post-intervention.

*Participants within the feasibility study will not be recruited as participants within the proposed future clinical trial in order to protect the scientific validity of the proposed future clinical trial, as the participants within the feasibility study will already have undergone the interventions, or similar interventions. However, participants within the feasibility study will likely not still be residents on the ward, as the average stay for participants on the ward is ~3.5 weeks. As such once the proposed future clinical trial has commenced, all participants within the feasibility trial will likely have left the ward well in advance.

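### Any significant ANOVA effect triggers post hoc testing, which puts the arm main effect, not an exercise effect, on a par with the contrasts that measure change

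*Protocol article*

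**What the plan says.** In the protocol article, Statistical methods (Secondary dependent variables) plans a 2×2 ANOVA for each secondary outcome. Its two factors are given as "the specially adapted resistance training intervention, and the MIOLI intervention, each with two levels: baseline and post-intervention". The testing rule follows: "A subsequent post hoc test will be utilised if a significant main effect or interactions are found". On thresholds and reporting it adds: "Significance levels will be set at 0.05 (p≤0.05), and effect sizes will be reported for all analyses". The section closes by promising an effect size and 95% CI with every result. It also lists means, medians, SDs and ranges as illustrative summaries, and asks for caution because the quantitative part is unpowered.

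The stated use of these analyses is to estimate efficacy in a way "useful to informing the design of the future powered clinical trial". Table 1 frames the limited-efficacy question as: "Is 2 weeks a sufficient duration to potentially provide significant benefit to patients".

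On design, the Sample size section says "This study aims to recruit a convenience sample of n =~30 participants: 15 in each intervention" and "No formal power calculations were conducted due to the feasibility nature of this study". The Design overview says there is no control group, that recruitment rolls over several months, and that "only one intervention will be run at a given time". No random allocation to arm is described. That the arms are not randomised is therefore an inference, not something the article states.

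**The concern.** An arm-by-time ANOVA gives three tests per outcome: arm, time, and arm by time. They answer different questions, but the trigger treats them alike.

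- **Arm main effect.** It compares the arms on the average of baseline and post-intervention values. If both arms change equally, or not at all, it shows only how the arms differed at the start. Arms filled in separate periods could well differ for reasons unrelated to exercise.
- **Post hoc test after a main effect.** Each factor has two levels, so the main effect already is the pairwise comparison. The follow-up repeats it.
- **Each arm's own change.** Without a control group, this and the between-arm difference in change are the quantities that bear on the Table 1 question. Under the rule, a test of each arm's change is run only when some omnibus effect reaches p≤0.05.

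At stake is how the pilot is read. A difference already present at entry could be taken as one programme doing better than the other. Changes picked out by the trigger would also be too large, on average, to plan the next trial on.

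**Working it through.** The article gives no power or derived sample size for these outcomes, so there is no stated figure to reproduce.

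**Inputs from the article:** 15 per arm; two time points; 0.05 per test (taken as two-sided).

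**Assumed, because the article gives no values:** normal outcomes with SD 1 at each time; baseline-post correlation ρ = 0.5, 0.7 or 0.8; a lasting difference d between the arms' populations; a true change δ, equal in both arms. The model is taken as a correctly fitted repeated-measures ANOVA, which favours the plan.

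**Step 1. Arm main effect when neither arm changes.** A person's mean of two values has variance (1+ρ)/2. The between-arm difference in these means has SE = √[(2/15)(1+ρ)/2] = √[(1+ρ)/15]. The test is a t test on 28 df with non-centrality d/SE.

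| d (SD) | ρ | SE | d/SE | P(arm effect significant) |
|---|---|---|---|---|
| 0.25 | 0.5 | 0.316 | 0.79 | 11.9% |
| 0.25 | 0.7 | 0.337 | 0.74 | 11.1% |
| 0.25 | 0.8 | 0.346 | 0.72 | 10.7% |
| 0.50 | 0.5 | 0.316 | 1.58 | 33.3% |
| 0.50 | 0.7 | 0.337 | 1.48 | 30.0% |
| 0.50 | 0.8 | 0.346 | 1.44 | 28.6% |

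**Step 2. Interaction in the same settings.** It compares mean changes, from which d cancels. Its expected value is 0 and it is significant in about 5% of analyses at any d. Simulation gives 4.7-5.3% for d from 0 to 0.8 SD.

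**Step 3. Any trigger when nothing is going on (d = 0, δ = 0).** 1 − 0.95³ = 14.3%; simulation gives 14.1-14.2%. This is three tests at 5%, as in any two-way ANOVA, and is not a defect in itself.

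**Step 4. What the trigger selects.** The mean change over both arms has SE = √[2(1−ρ)/30] = √[(1−ρ)/15], which is 0.183, 0.141 and 0.115 for the three correlations. With the 28-df critical value of 2.048, the time effect needs an observed change of about 0.37, 0.29 and 0.24 SD. Each exceeds a true change of 0.2 SD, so selection through the time effect pulls the estimate upward. Mean change among triggered analyses at δ = 0.2, from 40,000 simulated trials per setting:

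| Baseline difference d | ρ = 0.5 | ρ = 0.7 | ρ = 0.8 |
|---|---|---|---|
| 0 | 0.36 | 0.32 | 0.29 |
| 0.25 SD | 0.32 | 0.30 | 0.28 |
| 0.5 SD | 0.26 | 0.26 | 0.25 |

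The ratio to the truth runs from about 1.25 (0.25/0.2) to 1.8 (0.36/0.2). It falls as d grows, because an arm effect opens the gate without selecting on change.

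**Step 5. Why the SD of change matters.** With SD 1 at both times, the SD of change is √[2(1−ρ)] = 1.00, 0.77 and 0.63. Separate baseline and post-intervention SDs do not determine it. Its square, which drives a sample size based on change, runs from 1.0 to 0.4, a 2.5-fold range.

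**The case against.** **The critique assumes a model the article does not write.** Taken literally, each intervention is a factor with levels baseline and post-intervention. Each main effect would then be that arm's own change, and no arm main effect would exist. But two such factors cannot be crossed when each participant receives one intervention, so the literal layout is not workable. Arm by time is the only usable reading. The point depends on that reading and should say so.

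**Only the post hoc test is conditional.** This stands. A reader might infer that within-arm changes are reported only when they are significant. The article does not say that. The gate is any omnibus effect, including an arm effect unrelated to change, and effect sizes and 95% CIs are promised for all results. If the descriptive summaries are given by arm and time, each mean change follows by subtraction. What remains is that the within-arm change, its interval and its SD are not named among the results, and a follow-up that is never triggered yields no interval.

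**Contrast definitions may sit in an analysis plan not shown.** That is fair for any definition the article merely omits. The trigger sentence, however, is fixed in the text, and the point rests on it.

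**The two harms offset each other.** This also stands, as Step 4 shows: the larger the baseline difference, the smaller the inflation. The largest figures for both should not be quoted as if they occurred together.

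**The article already urges caution, and its primary outcomes are feasibility areas analysed qualitatively.** This limits the consequence. The caution concerns low power, though; it does not warn that an arm main effect is not an exercise effect.

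**Conclusion.** The point holds as a modest, cheaply removed weakness in a rule that the article states. On the arm-by-time reading, with 15 per arm and no change in either arm, an assumed baseline difference of 0.25 or 0.5 SD makes the arm effect significant in about 11-12% or 29-33% of analyses, against about 5% for the interaction. If the future trial's design used only triggered estimates, a true change of 0.2 SD would average about 0.25-0.36 SD. The article does not say that it would select estimates in this way.

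These figures rest on assumed baseline differences, correlations and changes, and on the inference that the arms are not randomised. Under randomisation with no effect, the arm test would itself reject in 5% of analyses.

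A reader might go further and conclude that the study will make a false efficacy claim or declare one programme superior. The text does not support that: it calls the efficacy testing limited and unpowered, and nowhere says how an arm main effect would be interpreted. The realistic consequence is misread pilot estimates.

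**What to change.** Replace the trigger sentence with two contrasts, reported for every secondary outcome whatever the p-value:

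- (a) each intervention's mean baseline-to-post change, with its 95% CI and the SD of change;
- (b) the between-intervention difference in change with its 95% CI, from the arm-by-time interaction or as the baseline-adjusted post-intervention difference, as the only between-arm contrast.

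State that the arm main effect will not be interpreted as efficacy, and drop the post hoc tests. Because (b) remains a comparison of arms run in different periods, keep the existing caution beside it.

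The cost is one or two sentences and a longer results table in which some intervals will be wide and unremarkable. No new data or participants are needed.
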